### Trial design

The VOYAGE trial is a prospective, randomized, multicenter open-label study with control group involving a total of eight centers. The research consortium includes both Academic (2 centers: Azienda Ospedaliero Universitaria Pisana e Azienda Ospedaliero Universitaria Senese) and non-Academic (6 centers: 2 located at Azienda Sanitaria Locale Toscana Nord Ovest, 2 at Azienda Sanitaria Locale Sud Est, 1 at Fondazione Toscana G. Monasterio, 1 at Teknon Medical Center—Heart Institute) hospitals located in Italy (n = 7) and Spain (n = 1). Some centers are involved in patient recruitment and cardiac imaging evaluation whereas others are also equipped for ablation procedures (5 centers). Teknon Medical Center – Heart Institute (Barcelona, Spain) is involved as an external research organization, with a training and technical support role, in particular regarding imaging dataset acquisition, post-elaboration and integration during ablation procedures. Centre will also participate on data analysis and result dissemination. The coordinating center is an Academic center located in Pisa (Azienda Ospedaliera Universitaria Pisana) with expertise in ventricular ablation procedures.

The study provides three arms:Group 1, Experimental: CMR guided ablation of the "anatomical" channels based on anatomical scarGroup 2, Experimental: CMR aided ablation of the "electrical" conducting channels (CCs) within the scarGroup 3, Standard of Care: Ablation guided by an electro-anatomical system

All patients who give informed consent for participation and fulfill the inclusion eligibility criteria will be consecutively enrolled (Inclusion and exclusion criteria are respectively shown in Tables 2 and 3). They will subsequently be evaluated for eligibility to CMR and CT. Patients with clinical or device-related contraindications to CMR or CT or with image quality deemed suboptimal for postprocessing will be assigned to Group 3 and undergo standard of care ablation. The other patients will be randomized in a 1:1 fashion to either Group 1 or 2 using a web-based platform. The scientific coordinator of the study or a delegate should be the unique responsible of randomization and will be contacted upon all new recruitments. LGE-CMR data obtained by 1.5 or 3 T CMR and multi-detector cardiac tomography (MDCT) data obtained using a 64 to 128 slice CT scanner will be processed with a specific commercial software (ADAS 3D, Galgo Medical, Barcelona, Spain). In Group 1, ablation will be performed based only on cardiac imaging information processed by the abovementioned software without electroanatomical mapping. A so-called anatomical approach is consistent with a previous observation [9] that ablation of channels only can be effective in preventing VA recurrences. In Group 2 ablation procedure will be based on information derived from both imaging and electroanatomic mapping data, but electrical CCs will remain as the final ablation target. Finally, Group 3 will be treated with standard ablation according to current clinical practice based on electroanatomic mapping (EAM). (Fig. 1).

**Table 2 Tab2:** Study inclusion criteria

Inclusion criteria
Indication for VT ablation in patients with structural heart disease (indications according to the 2015 ESC Guidelines for the management of patients with ventricular arrhythmias and the prevention of sudden cardiac death);
Structural heart disease (clinical history, ECG, multimodality imaging) involving the left ventricle
Signed informed consent;

**Table 3 Tab3:** Study exclusion criteria

Exclusion criteria
Age < 18 years;
ICD not already implanted nor expected within 1 month;
High probability of non-adherence to the follow-up requirements (due to social, psychological, or medical reasons);
Inability to give written informed consent;
Pregnancy (suspected or confirmed);
Acute coronary syndrome or PCI in the previous 30 days
Creatinine clearance < 15 ml/min (stage 5 CKD) (according to clinical history or out/in-patient tests performed upon enrollment)
Severe chronic liver disease (Child–Pugh score C) (according to clinical history or out/in-patient tests performed upon enrollment)
Heart surgery for valve disease in the previous 6 months or expected within 6 months
Coronary artery bypass graft in the previous 3 months
NYHA functional class IV heart failure or CCS functional class IV angina
Previous VT ablation
Systemic illness likely to limit survival to < 1 year

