## Methods

### Study hypothesis and primary endpoint

Our hypothesis is that a comprehensive preprocedural individual characterization of the myocardial substrate via a CMR scan, and its integration within the mapping system can significantly improve technical intervention and patient outcome. The primary objective is to analyze the outcome of CMR guided/aided approaches of VT ablation in terms of effectiveness at 12 months in comparison to a control group (standard of care VT ablation). The primary endpoint is defined as any VT recurrences during a 12-months follow-up (not including the first month). VT episodes will be considered as recurrences if sustained (more than 30 s) or requiring appropriate ICD intervention and will be detected during outpatient clinic evaluation through an ICD interrogation.

Pre-specified group subanalyses will compare in terms of the primary endpoint:Patients with structural heart disease of ischemic originPatients undergoing endocardial-substrate only ablation

Secondary objectives are shown in Table 1.

**Table 1 Tab1:** Secondary endpoints

Secondary endpoints
Health-related quality of life changes
Procedural time (introducer in-introducer out)
Fluoroscopy duration
X-ray exposure
Radiofrequency time
Number of RF applications
VT inducibility at the end of ablation with number of residual VTs
Appropriate and inappropriate ICD interventions (ATP or shocks) anytime and after 1 month
Rate of patients with contraindication to CRM or with poor CMR imaging
Hospital admission for cardiac causes
VT storm anytime and after 1 month
Composite endpoint including death at any time, VT storm and appropriate ICD shock after 1 month of treatment
*Complications during 12-month follow-up*
Death (related or not to the procedure)
Myocardial infarction
Stroke or transient ischemic attack (TIA)
Other thromboembolic events
Cardiac perforation or tamponade
Vascular complications
Prolonged or repeat hospitalization
Heart block
Pericarditis requiring intervention
Pneumothorax
Pulmonary edema
Hepatic injury
Abdominal issues

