### Sample size and statistical analysis

To test the primary hypothesis, 103 patients will be necessary with 80% power and 5% type 1 error, considering 50% of group 1–2 (low risk), 50% of group 3 (high risk), 16% of likelihood of VT recurrences at 12 months in low-risk patients and 44% of likelihood in high-risk patients with HR (high risk/low risk of recurrences) of 2.75 (Cox PH, 2-sided equality).

All applicable statistical tests will be 2-sided and will be performed using a 5% significance level. Continuous variables will be reported as mean ± standard deviation, or median (range or interquartile range if data are skewed) if not normally distributed; these variables will be compared using Student’s t-test if normally distributed, Aspin-Welch test if normally distributed with unequal variance demonstrated using Variance-ratio F-test, or Mann–Whitney U test if not normally distributed. Categorical variables will be expressed as total number (percentage) and will be compared by chi-squared test. As far as the primary endpoint, data will be analyzed according to the intention-to-treat principle. Survival free from ventricular arrhythmia, will be evaluated using a time-to-first-event analysis with the Logrank test and the Kaplan–Meier cumulative event rate. A multivariable Cox proportional hazards model will be performed to investigate the effects of baseline characteristics in predicting ablation results.

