## Discussion

Integration of high-definition myocardial substrate data acquired via imaging techniques such as CMR and MDCT has already been proved as a feasible and potentially effective solution for VT ablation, even in complex and cutting-edge scenarios [9, 12–14]. However, MDCT-only approaches, in which myocardial wall thickness maps can identify "CT-channels" [15] where VT functional isthmuses can be located, showed poor performance [16] when compared to CMR in correctly identifying the arrhythmogenic substrate, especially when entirely subendocardial.

The mainstay of our proposal is represented by real time integration, alignment, and synchronization of 3D-meshes, containing anatomical data obtained from MDCT, and substrate data derived from postprocessed CMR, with the tridimensional references of the electroanatomical mapping suite, allowing operators to effectively navigate such meshes irrespectively of the presence of a standard complete LV EAM.

As far as CMR is concerned, single-center experiences have already shown that an approach where MRI derived information is used alongside EAM data, to aid VT ablation ("MRI-aided"), may lead to improved efficacy over traditional EAM-only techniques [12, 17]. The natural evolution of such method may be represented by “MRI-guided” approaches, where EAM acquisition is completely avoided, and the operator relies solely on imaging data; a single-center nonrandomized study demonstrated that this approach is not only feasible and safe, but could lead to lower acute VT inducibility rates and comparable long-term efficacy with “MRI aided” procedures, while allowing more efficient procedures, with lower procedure duration and radiological exposure [9].

The primary objective of this study is to verify, for the first time in a multicenter controlled open-label clinical trial, whether CMR guided and aided strategies, as a whole, truly represent a more effective, more efficient, and at least as safe, if not safer, VT ablation approach when compared to the standard EAM-only guided technique. A confirmation of our primary hypothesis can also lead to the speculation that an imaging-based workflow could better standardize the approach to VT’s substrate, finally determining less variability between operators and a smoother) VT ablation learning curve, as compared to EAM only technique.

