While not powered for this specific objective, our study could also reveal whether a complete anatomical CMR-derived substrate elimination, as established for CMR-guided (“Group 1”) procedures, could guarantee better long-term results. The present trial was designed to overcome most of limitations related to the implementation of our proposed approach
. First, the incidence of treatable VA is relatively low in general population and high volume (of cases) is critical for both imaging elaboration and ablation procedures. Accordingly, we created a network of centers, each with at least one major expertise, and a period of training before the trial (6 months) has been devoted to share information about image acquisition and ablation approaches. Eventually, a total of four centers for CMR acquisition and five centers for ablation were able to provide high quality activities, with a definite standardization of CMR sequences and treatment. The most critical process, represented by standardization of imaging acquisition protocols, has been guaranteed and supervised by the core laboratory, in collaboration with the aforementioned external research organization.

In conclusion, VOYAGE is the largest trial so far to propose and test, in a randomized setting, a comprehensive workflow for CMR-guided/aided VT ablation. If positive, results from this study could be applied in large scale in the electrophysiology practice, contributing to the adoption of substrate-tailored approaches, coherently with current trends in the era of precision medicine.

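### The primary comparison (Groups 1–2 vs Group 3) is not randomised, yet it is tested by a log-rank test with no stated adjustment, under an intention-to-treat label, in a trial described as randomised

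*Protocol article*

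**What the plan says.** All places are in the protocol article.

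- **Allocation (Trial design).** "Patients with clinical or device-related contraindications to CMR or CT or with image quality deemed suboptimal for postprocessing will be assigned to Group 3". Then: "The other patients will be randomized in a 1:1 fashion to either Group 1 or 2 using a web-based platform".
- **Primary objective (Study hypothesis and primary endpoint).** It is "to analyze the outcome of CMR guided/aided approaches of VT ablation in terms of effectiveness at 12 months in comparison to a control group". The Discussion confirms that the two CMR arms are pooled; it asks "whether CMR guided and aided strategies, as a whole, truly represent a more effective, more efficient, and at least as safe".
- **Randomised contrast.** Guided versus aided ablation is a secondary endpoint in the Abstract, and the Discussion says the study is not powered for it.
- **Analysis (Sample size and statistical analysis).** "As far as the primary endpoint, data will be analyzed according to the intention-to-treat principle". The test is a log-rank test on time to first event, with Kaplan–Meier rates; no stratification, weighting or adjustment is mentioned. The only multivariable model is described thus: "A multivariable Cox proportional hazards model will be performed to investigate the effects of baseline characteristics in predicting ablation results".
- **Sample size (same section).** 103 patients for 80% power at two-sided 5%, with 12-month recurrence of 16% versus 44% and a hazard ratio of 2.75.
- **Description of the trial.** The Abstract and Trial design call the study randomised. The Discussion closes with: "VOYAGE is the largest trial so far to propose and test, in a randomized setting, a comprehensive workflow for CMR-guided/aided VT ablation".

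**The concern.** No patient in the primary comparison is randomised between the treatments being compared. A patient is a control because of a clinical or device-related contraindication, or because the images could not be used. These features may go with prognosis, and nothing in the design balances them. The log-rank test sees only the sum of any treatment effect and any difference in case mix.

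Followed as written, a case-mix difference could be reported as an effect of CMR guidance from a randomised trial, with a p-value whose 5% error rate depends on the two kinds of patient having equal prognosis. The article says that a positive result could be applied on a large scale, so the strength of this claim matters.

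**Working it through.** **1. The plan's own figure.** Inputs from the sample size section: hazard ratio 2.75, equal group shares, rates 16% and 44%, two-sided 5%, 80% power.

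- Events (Schoenfeld): (1.960 + 0.842)² / (0.25 × (ln 2.75)²) = 30.7.
- Mean event rate: (0.16 + 0.44)/2 = 0.30.
- N = 30.7/0.30 = 102.3, rounded up to 103. This reproduces the stated number with no dropout.
- At N = 103, expected events are 103 × 0.30 = 30.9 and power is 80.3%.

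The arithmetic is sound. It attributes the whole of the 16% versus 44% difference to treatment.

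**2. Rejection rate with no treatment effect.** Let c be the hazard ratio of imaging-unsuitable versus suitable patients from prognosis alone. The document does not give c; the values below are assumptions. The log-rank z has mean m = √(30.9 × 0.25) × ln c = 2.78 × ln c, and the rejection rate is Φ(m − 1.96) + Φ(−m − 1.96).

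| c (assumed) | Formula | Simulation (20,000 runs, 103 patients, pooled risk 30%) |
|---|---|---|
| 1.0 | 5.0% | 4.8% |
| 1.25 | 9.5% | 9.3% |
| 1.5 | 20.3% | 20.0% |
| 2.0 | 48.7% | 47.1% |
| 2.75 | 80.3% | not run |

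If c exceeds 1, nearly all of the excess favours CMR. If c is below 1, the formula is symmetric in ln c and the bias runs the other way, masking a real benefit. Equally, an observed hazard ratio of 2.75 would leave 2.75/1.5 = 1.83 for treatment if c were 1.5, and 2.75/2 = 1.38 if c were 2.

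**3. What imbalance would produce such values.** Take one binary risk factor with hazard ratio h and prevalence p in Groups 1–2 and q in Group 3. Then c is roughly (1 + q(h − 1)) / (1 + p(h − 1)). All inputs are assumed. The simulated rates come from 6,000 runs each with no CMR effect; a range shows two separate runs.

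| p vs q | h | Implied c | Simulated rejection |
|---|---|---|---|
| 30% vs 40% | 2 | 1.4/1.3 = 1.08 | 5.0% |
| 30% vs 50% | 1.5 | 1.25/1.15 = 1.09 | 6.0% |
| 20% vs 40% | 2 | 1.4/1.2 = 1.17 | 6.8% |
| 20% vs 60% | 2 | 1.6/1.2 = 1.33 | 11.6–12.5% |
| 20% vs 60% | 3 | 2.2/1.4 = 1.57 | about 24% |
| 10% vs 60% | 3 | 2.2/1.2 = 1.83 | about 36% |

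Mild imbalance in a single factor does little harm. Strong imbalance, or several factors pointing the same way, does a great deal.

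**4. Power after adjustment.** Let R² be the share of group membership explained by the covariates (assumed), with an adjusted hazard ratio of 2.75. Power is Φ(√(30.9 × 0.25 × (1 − R²)) × ln 2.75 − 1.96), and N for 80% power is 102.3/(1 − R²).

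| R² | Power at 103 | N for 80% |
|---|---|---|
| 0 | 80% | 103 |
| 0.1 | 76% | 114 |
| 0.2 | 71% | 128 |
| 0.3 | 65% | 147 |

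**The case against.** **The rule is disclosed.** The Abstract and Trial design state how Group 3 is formed, the study does contain a randomisation, and the Discussion calls the trial controlled where it states the primary objective. This stands: nothing is concealed. It does not justify the closing claim of a test in a randomised setting.

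**Intention-to-treat has content.** It can mean analysis as assigned, and it applies properly to Group 1 versus Group 2. This stands. A reader might infer that the term is meaningless here, which goes too far; for the primary contrast it simply carries no protection from randomisation.

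**Risk labels.** A reader might take "considering 50% of group 1–2 (low risk), 50% of group 3 (high risk" as an admission that controls have a worse baseline prognosis. The text does not support that: the labels are tied to the planned 16% and 44% recurrence rates and may only name the expected rate under each approach.

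**Certain inflation.** A reader might infer that the 5% error is known to fail, or to fail in favour of CMR. The document gives no case-mix data. The exclusion criteria narrow the population, and patients with an MRI-conditional ICD can be scanned, so having a device does not by itself decide the group.

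**Imaging failures.** A reader might say that failures of the CMR strategy are charged to the control arm. That presumes a question about the imaging strategy. Patients with poor images do receive standard ablation, and Table 1 reports their rate together with contraindications.

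**An unseen SAP could add adjustment.** It could. It cannot make this contrast randomised, and the article already names the log-rank test for the primary endpoint.

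**Conclusion.** Wrong as written. The primary contrast lacks a property that the article claims for the trial: it is a non-randomised comparison in which group and imaging suitability coincide by rule. The log-rank test holds its 5% level only if suitable and unsuitable patients have the same prognosis, which the document neither shows nor secures. The size of the problem is a range, not an estimate: about 5% to 49% rejection with no treatment effect for assumed prognostic hazard ratios from 1.0 to 2.0. The sample size arithmetic is correct, and the sole randomised comparison, Group 1 versus Group 2, is unaffected.

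**What to change.** 1. **Labels and claim.** Describe Groups 1–2 versus Group 3 as a non-randomised controlled comparison, limit its conclusion to association, and state that confounding by imaging suitability cannot be removed. Reserve the word randomised for Group 1 versus Group 2. Say that intention-to-treat means only analysis as assigned for the primary contrast.
2. **Primary estimate.** Use a group effect from a Cox model adjusted, or weighted by propensity score, for a few pre-specified variables available from baseline demographics, history and echocardiography, such as age, LVEF and ischaemic aetiology. Keep the log-rank test as supportive. The list must be short: three covariates plus group give 30.9/4 = 7.7 events per parameter, and adding centre (five ablation centres, four indicators) would leave 30.9/8 = 3.9. Table 4 does not name VT storm, has no ICD check at baseline and schedules CMR only for Groups 1 and 2, so these should not be assumed available as covariates.
3. **Group 3 by reason.** Report contraindicated patients separately from those imaged with poor quality. Add a sensitivity analysis by imaging strategy, labelled as a different question because the poor-image patients received standard ablation.
4. **Power.** Restate it for the adjusted analysis, with the assumed R².

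The cost is text, a few derived variables, a weaker claim and a wider interval: about 76% to 65% power at 103 patients for R² of 0.1 to 0.3. Adjustment reduces bias from the listed variables only. A randomised answer would need imaging-suitable patients to be randomised to standard ablation as well, which is a different design.

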**Fig. 1 Fig1:**
[figure not shown]
Study design flowchart. VT: ventricular tachycardia; MDCT: multidetector computed tomography; CMR: cardiac magnetic resonance

### Preprocedural CT scan

In absence of contraindications, a contrast-enhanced multi-detector cardiac tomography (MDCT) will be obtained using a 64 or 128 slice CT scanner, with ECG gating set between 50 and 100% of cardiac cycle. The exam will be performed after hospital admission or in an outpatient setting. Anatomical data obtained from such exam will be used for clinical management purposes and, after post-elaboration with ADAS 3D software, integrated within the spatial reference coordinates of the EAM system (CARTO 3 Biosense Webster, Diamond Bar, CA, USA), alongside data derived from LGE-CMR.

### Preprocedural CMR scan

In absence of contraindications, an LGE-CMR will be obtained using a 1.5 or 3 T scanner. In patients already implanted with an MRI-conditional ICD, the exam will be performed using a 1.5 T scanner using a specific wideband sequence in order to avoid device-related artifacts. CMR machines in use at participating centres at time of publication are: Magnetom Avanto 1.5 T (Siemens Healthcare, Erlangen, Germany), Magnetom Aera 1.5 T (Siemens Healthcare, Erlangen, Germany) and Signa Artist 1.5 T (GE Healthcare, Chicago, IL, USA). Anatomical data obtained from such exams will be used for clinical management purposes and, after post-elaboration with ADAS 3D software, integrated within the spatial reference coordinates of the electroanatomical mapping system (CARTO 3 Biosense Webster, Diamond Bar, CA, USA), alongside anatomical data derived from MDCT.

### Image processing

Images processing (ADAS 3D Galgo Medical, Barcelona, Spain) is pivotal to translate radiomics data produced by CMR into utilizable maps within the electrophysiology lab. Briefly, sequence packs created within each center will be transferred and processed by core-lab and finally elaborated by the software with the purpose of being integrated with the ablation mapping suite (CARTO 3, Biosense Webster, Diamond Bar, CA, USA). A pre-study phase for the achievement of quality standards in images acquisition has been accomplished in every center before the enrollment start date. The core-lab for image processing (U.O. Cardiologia 2—Azienda Ospedaliero Universitaria Pisana), will be further supported, if required, by Heart Institute in Teknon Medical Center (Barcelona, Spain). A VPN tunnel and an SFTP server will be used to securely transfer anonymized data between centers for post-elaboration.

LV endocardial and epicardial borders will be delimited by an experienced operator with a semiautomatic segmentation algorithm. Nine concentric layers will be identified from endocardium to the epicardium (10 to 90% of wall thickness). LGE-CMR information will be projected using trilinear interpolation over each layer surface and signal intensity distribution will be color-coded. Scar core (SC) and border zones (BZ) will be defined as 40% ± 5% and 60% ± 5% of maximum signal intensity respectively. Heterogeneous tissue channels (HTCs) will be defined as a corridor of BZ between two core areas or between a core area and a valvular annulus connecting two areas of healthy tissue.

The software will identify HTCs automatically, and they will be classified as:Sub-endocardial (layers from 10 to 50%).Sub-epicardial (layers from 60 to 90%).Transmural (layers from 10 to 90%).

Pixel signal intensity (PSI) maps and HTCs derived from LGE-CMR studies will subsequently be fused and aligned with the anatomical reconstructions extracted from multidetector cardiac tomography (MDCT) using the ADAS 3D software platform. This alignment allows the integration within the spatial reference coordinates of the mapping system by performing a fast anatomical mapping of the aortic root [9].

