### Ablation procedure

Ablation procedure will be carried out in an electrophysiology lab by using an electroanatomical mapping system (CARTO 3, Biosense Webster, Diamond Bar, CA, USA). An open irrigated 3.5 mm tip radiofrequency catheter (ThermoCool SmartTouch SF, Biosense Webster, Diamond Bar, CA, USA) will be used both for mapping and ablation.

In Groups 1 and 2 fast anatomical mapping (FAM) of the aorta from the aortic root to the origin of the left subclavian artery will be obtained in order to align such reconstruction with the MDCT-derived 3D model of the aorta and left ventricle, thus enabling the alignment between CARTO spatial references and post-processed CMR derived 3D model.

An electroanatomical map (EAM) of the target chamber will be obtained only in groups 2 and 3. EGMs will however be analyzed in all cases to avoid applications:At the level of His or fascicular EGMsAt the level of EGMs with an amplitude > 3 mV or 1.5–3 mV without delayed components, during sinus rhythm of after application of multiple extrastimuli to check for the presence of hidden slow conduction.

The target for RF ablation changes accordingly to the group of allocation or randomization.

Group 1: RF energy will be delivered at the entrance of HTCs identified in the maps created by images processing, regardless of the presence of any pathological electrogram (EGM) at such locations (Fig. 2). If VT is spontaneously induced, it’s allowed to map the circuit and ablate during tachycardia, even though it’s suggested to acquire the template and stop the arrhythmia (at first appearance) and continue the ablation of substrate.

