**Fig. 2 Fig2:**
[figure not shown]
Mapping suite showing a CMR-guided procedure, with VT interruption during RF delivery at an heterogeneous tissue channel **(**HTC**)** on 3D CMR model. Green: MDCT-derived aorta 3D model, blue areas: healthy tissue, red areas: scar tissue, yellow areas: border zone

Group 2 and Group 3: Ablation sites will be identified after analyzing the complete EAM, targeting conducting channel entrance-compatible EGMs, according to the “scar dechanneling” technique [10]. Other techniques aimed at achieving complete substrate ablation and currently used by the centre performing VT ablation, will be accepted. In case of absence of electrograms with delayed components at EAM, VT will be induced, and mapping will be done to delineate the circuit. In Group 2 the scar area localization via CMR images integrates the EAM data to help in substrate delineation focusing on that area. In Group 3 a complete left ventricle EAM will be achieved.

At the end of ablation, we will verify the absence of pathological EGMs and we’ll proceed towards inducibility test. In case of VT induction, we could have 2 scenarios: (1) hemodynamically tolerated VT: it will be mapped and ablated; (2) not hemodynamically tolerated VT: VT template will be taken and, after its interruption, used for pacemapping to identify VT exit site, which will undergo ablation.

Acute success will be defined as non-inducibility (2 drives, 2 sites, up to 3 extrastimuli) of any sustained monomorphic VT at the end of the procedure. Partial success will be considered with the clinical VT successfully ablated with other monomorphic VTs remaining inducible. Pre-ablation inducibility is not required and is discouraged unless in the abovementioned conditions.

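### The scar-core and border-zone cut-offs are printed in reverse order, so the channel definition that sets the Group 1 ablation target is wrong as written

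*Protocol article*

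**What the plan says.** All references are to the Methods of the protocol article.

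- **Cut-offs (Image processing).** "Scar core (SC) and border zones (BZ) will be defined as 40% ± 5% and 60% ± 5% of maximum signal intensity respectively". The last word fixes the pairing: core with 40%, border zone (BZ) with 60%. No other section gives cut-offs. The Fig. 2 legend assigns colours to healthy tissue, border zone and scar, but no values.
- **Channels (Image processing).** A heterogeneous tissue channel (HTC) is "a corridor of BZ between two core areas or between a core area and a valvular annulus connecting two areas of healthy tissue". Detection is left to the program: "The software will identify HTCs automatically".
- **Use in Group 1 (Ablation procedure).** "RF energy will be delivered at the entrance of HTCs identified in the maps created by images processing", whether or not a pathological electrogram is present there. An electroanatomical map (EAM) "of the target chamber will be obtained only in groups 2 and 3", so Group 1 has none.
- **Electrical input that remains in Group 1 (Ablation procedure).** There are exclusion rules for electrograms ("EGMs will however be analyzed in all cases to avoid applications" at certain sites). If VT arises, the operator is "allowed to map the circuit and ablate during tachycardia". The end-of-procedure electrogram check and inducibility test are not restricted to particular groups; if VT is induced, the rule for one scenario is "hemodynamically tolerated VT: it will be mapped and ablated".

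**The concern.** HTCs are built from two tissue classes, core and BZ. If the limits of those classes are exchanged, the corridors found from them are not the corridors that the protocol describes. In Group 1 the entrances to those corridors are where energy is planned, and there is no chamber map to set against them. The electrical checks that remain can withhold or add lesions, but none of them reclassifies tissue on the imaging map.

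Two things are at stake. The certain one is reproducibility: the article hopes for large-scale use of the workflow, and a centre that copied the printed thresholds would copy a reversed definition. The uncertain one is conduct: recruitment began in June 2021 (Trial status), so it is worth one check that the settings in use were in the right order.

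**Working it through.** The thresholds are a definition, not a computed statistic, so the check is one of consistency.

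**Step 1: the order that the article requires.** Two statements settle it.
- The modality is late gadolinium enhancement, and the quantity thresholded is its signal intensity. Scar is the enhanced tissue, so core must be brighter than healthy tissue.
- By the HTC definition, BZ forms the corridor that runs between core areas and joins healthy tissue on both sides. BZ is therefore the intermediate class.

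Together these give healthy < BZ < core. The HTC definition alone makes BZ intermediate; the direction comes from enhancement.

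**Step 2: the order that is printed.**
- Core: 40 ± 5 = 35 to 45% of maximum.
- BZ: 60 ± 5 = 55 to 65% of maximum.
- The highest core value (45) is below the lowest BZ value (55), so the tolerance cannot restore the order.

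**Step 3: possible readings.** The sentence has no greater-than or less-than sign, so the natural readings are set out here.
- *Lower limits:* core 40–60%, BZ from 60%. The brightest tissue is called border zone.
- *Upper limits:* core up to 40%, BZ 40–60%, healthy above 60%. BZ is intermediate, but core is the dimmest class and healthy tissue the brightest, which contradicts enhancement.
- *Centres of bands:* core 35–45%, BZ 55–65%. BZ is brighter than core, and tissue near 100% of maximum is in neither class.
- *Mixed limits:* core from 40% upward, BZ up to 60%. Tissue between 40% and 60% is then both. The defect here is overlap, not reversal, but the definition is still unusable.

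**Step 4: exchange the two values and read them as cut-offs.**

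| Signal (% of maximum) | As printed, lower limits | Values exchanged |
|---|---|---|
| 30 | healthy | healthy |
| 50 | core | BZ |
| 80 | BZ | core |
| 100 | BZ | core |

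With the values exchanged, BZ lies between healthy tissue and core, as Step 1 requires.

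**Step 5: how many patients depend on the core/BZ split.** Inputs are the total of 103 and the 50% share for Groups 1 and 2 combined (Sample size and statistical analysis), and 1:1 randomization between those groups (Trial design).
- Group 1: 103 × 0.5 × 0.5 = 25.75, about 26.
- Group 2 is not counted. Its final target remains the electrical conducting channels, and imaging serves to locate the scar area. If the values are lower limits, core and BZ together are everything from 40% upward under either labelling, so that area does not change.

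**Step 6: the sample size is not touched.** Schoenfeld events for two-sided 5%, 80% power, HR 2.75 and equal groups: (1.960 + 0.842)² / (0.25 × (ln 2.75)²) = 30.68. The mean event rate is (0.16 + 0.44)/2 = 0.30. Then 30.68/0.30 = 102.3, rounded up to 103. The stated figure reproduces, and no threshold enters it.

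**The case against.** The strongest reply is that this is a slip of the pen. Channels are found automatically by a named commercial program, processing goes through one core-lab with outside technical support if needed, and six months of training preceded the trial. The Fig. 2 legend describes VT stopping while energy was delivered at an HTC. That is a single case and says nothing about thresholds, but it gives no hint of a mislabelled target. The image-processing account is also openly abbreviated, and the full protocol is not shown.

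Most of this stands. A transposition in the write-up is the likeliest explanation, and the fault is established for the article's wording only. It does not remove the point: the article does not leave the definition to another document but states it, and states it wrongly.

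A reader might infer three stronger things that the article does not support.
- *That Group 1 patients were ablated at the wrong sites.* No settings or maps are reported, and the electrogram exclusions (His or fascicular signals, amplitude above 3 mV, or 1.5–3 mV without delayed components) would keep some wrong sites from being treated.
- *That every patient with an imaging map is affected.* For Group 2 this fails, for the reason in Step 5 of the working.
- *That patients treated from a reversed map would be protocol deviations.* Such a map would follow the only text shown, so the label presumes a correct definition in a document not seen.

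**Conclusion.** The point holds as an error in the text: core and BZ carry each other's values, against both the meaning of enhancement and the article's own channel definition, and no other section corrects it. It is more than cosmetic, because these are the operating thresholds behind the planned target of one experimental arm, and it should be corrected.

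Its reach is limited. It concerns mainly Group 1, about 26 patients, and their treatment only if the printed order was actually used. That number rests on the 50% planning share; actual group sizes follow imaging suitability and are not fixed. No effect on VT recurrence is claimed.

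The order can be inferred from the article. The exact band structure cannot, because the article does not say whether the values are cut-offs or bands and gives no limit for healthy tissue.

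**What to change.** - **Text.** In Image processing, exchange the two values so that BZ is the intermediate class. The most natural form is BZ from 40% ± 5% to 60% ± 5%, and scar core above 60% ± 5%, of maximum signal intensity. The core-lab should confirm the exact wording.
- **Settings.** The core-lab confirms that the software settings used since June 2021 follow this order.
- **If any map was made in the reversed order.** Report those patients and keep them in the intention-to-treat analysis.

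The cost is one corrected sentence and one check of settings. If the settings prove correct, nothing changes in procedures, patients, sample size or analysis.
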